### Study schedule (timing of events)

All individuals from the SCOOP program will be screened for eligibility inclusion and exclusion criteria 6 months before their guideline dictated surveillance colonoscopy. Any individuals that do not respond to study invitation more than 2 months prior to their scheduled surveillance colonoscopy will be excluded from the study. Prior to enrollment, the participant is given a verbal description of the study in detail and are informed that the selection of the study arm is random. Any participant not willing to be assigned to the delegated study arm, either before or after informed consent, will be excluded from the study. If the patient consents to be enrolled and then subsequently withdraws, they will still have their colonoscopy following guideline recommendations.

After obtaining informed consent, all individuals will be sent two surveys (survey 1 and survey 2) by mail prior to them being informed of their randomization (Table 1). Survey 1 will establish baseline quality of life (QOL) using the validated EQ-5D instrument [35] and assess consumer preferences for surveillance strategies and health and psychological predictors of attitude to different protocols. Survey 2 will explore consumer preferences for test attributes using discrete choice experiments (DCE). Upon return of surveys 1 and 2, all participants will be sent a letter by mail informing them of their randomization arm. For those participants who are randomized to the intervention arm, a letter will be sent to their primary health care physician informing them of the change to their patients’ surveillance colonoscopy timing. The QOL survey will be repeated 4 weeks after the participant completes their colonoscopy (survey 3), along with completion of a costings survey (survey 4) within 2 weeks after colonoscopy to determine the costs (direct and indirect) involved with undergoing surveillance (such as time off work, transport costs, support person’s costs, out-of-pocket expenses for colonoscopy, cost of adverse events). Each survey will take less than 20 min to complete. Within the follow-up test preference and QOL survey (survey 5), which is provided one month after colonoscopy, there will also be questions to ascertain satisfaction with the surveillance procedure that they just completed. Finally, a follow-up DCE survey (survey 6) will repeat the DCE survey performed before colonoscopy, once the patients have been informed of pathology findings from their colonoscopy.

**Table 1 Tab1:** Study schedule listing the timing of events (in months) relative to the guideline recommended colonoscopy due date specified at the time of enrolment

	**Screening/enrolment**	**Survey 1 and survey 2**	**Randomization**	**On-time colonoscopy**	**FIT 1**	**FIT 2**	**Delayed colonoscopy**	**Survey 5**	**Survey 6**
Control	− 6	− 3	− 2	0	N/A	N/A	N/A	7	8
Intervention: 3-year surveillance	− 6	− 3	− 2	N/A	0	N/A	12	13	14
Intervention: 5-year surveillance	− 6	− 3	− 2	N/A	0	12	24	31	32

Two-sample OC-Sensor FIT kits (Eiken Chemical Company, Tokyo, Japan) will be sent annually only to participants who are enrolled into the intervention arm, on their original guideline scheduled surveillance colonoscopy due date. Participants on a 5-year surveillance and with a 2-year delay will receive two FIT kits (1 each year). Participants on a 3-year surveillance will receive one FIT. The colonoscopy procedure will be performed on-time (control group — no FIT required) or on the delayed due date (Intervention group) if the interval FIT is negative (i.e., < 20 µg Hb/g feces). Any participants presenting with symptoms will be scheduled for colonoscopy as soon as possible regardless of trial intervention and will be withdrawn from the study. At the completion of the study and collection of all data, analysis will be performed to determine the primary and secondary outcomes.

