### Enrolment criteria

Inclusion criteria for enrolment into the study include:Males and females enrolled in the SCOOP surveillance colonoscopy program.Aged older than 18 years of age.Individuals who have either had a previous colonoscopy finding of adenoma, or who have a significant family history of CRC [32].Individuals due for surveillance colonoscopy within the next 6 months after a recommended interval of three or five years.Individuals with a low FIT Hb concentration (< 2 μg Hb/g feces) within the last 3 years of their next scheduled colonoscopy.

Exclusion criteria encompass the following:Individuals with a familial syndrome of CRC or inflammatory bowel disease (IBD).Individuals with a personal history of CRC or sessile serrated lesions.Individuals scheduled for colonoscopy for any indication other than surveillance.Inability to understand study information and give informed consent.

Endoscopist exclusion criteria for this study will be:Not listed as an investigator on the study (for private sector hospital endoscopists).Not performing colonoscopy at a participating hospital.

Individuals with a low FIT Hb result (i.e., < 2 µg of Hb per g of feces) which was completed up to 3 years before their scheduled colonoscopy will be stratified for current colonoscopy interval (i.e., 3 or 5 years). Each group will be randomly assigned (1:1) to intervention or control. Intervention will extend surveillance colonoscopy interval by approximately one third:If guideline sets a 3-year surveillance interval (as usually recommended following an advanced adenoma [32]), the interval will be extended to 4 years.If guideline sets a 5-year surveillance interval (as usually recommended following a non-advanced adenoma or no neoplasia [32]), the interval will be extended to 7 years.

An interval is considered to have been appropriate if done within 6 months of the set time [33, 34].

Randomization will be performed using the stratified method with block randomization, controlling for (1) the referring endoscopic specialist, (2) the participating private or public hospital, and (3) the recommended surveillance interval. Participants and referring endoscopists will not be blinded to the randomization arm. Those not randomized to the Intervention group will receive standard clinical care, following the Australian National Health and Medical Research Council (NHMRC) guidelines for colonoscopy surveillance intervals [32].

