### Outcome parameters (endpoints)

Primary outcome:Incidence of advanced neoplasia (advanced adenoma or CRC) in the control and intervention groups.

Secondary outcomes:Incidence of complications from colonoscopy (admissions for bleeding or perforation, or death).Risk factors associated with advanced neoplasia including age, sex, family history of CRC, previous history of adenoma, number of prior colonoscopies.Cost-effectiveness of a modified surveillance frequency using interval FIT compared to standard surveillance practice.Acceptability to consumers of changes to the surveillance strategies and the variables that predict this attitude.

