### Statistical analyses

#### Advanced neoplasia incidence

Colonoscopy outcomes of the intervention group will be compared to those from the control group. Incidence of advanced neoplasia (CRC and advanced adenoma), non-significant adenomas, non-neoplastic lesions, and normal outcomes will be compared between groups with univariate (Fisher’s exact and chi-squared test). Odds ratios will be calculated from logistic regression analysis to assess factors associated with the development of advanced neoplasia, adjusted for risk factors associated with neoplasia development such as age, sex, and the original surveillance interval. To account for non-adherence of the timing for the surveillance colonoscopy in the study arm (e.g., colonoscopy was brought forward due to a positive FIT or symptoms), alternative analyses will be incorporated such as per-protocol, modified intention-to-treat, or as-treated, alongside the primary intention-to-treat analysis.

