#### Consumer acceptability

Overall preference for and satisfaction with surveillance type and frequency scenarios will be assessed by direct questions and the DCEs, giving different scenarios of methodology (colonoscopy with or without FIT), frequency, and effectiveness. Themes analyzed include (1) how acceptable they find a modified protocol, (2) how likely they would be to comply with it, and (3) how anxious the changes would make them. The collected demographic and clinical variables will be used to determine if there are any associations with surveillance preferences, and these will include: sex, age, number of previous colonoscopies, number of previous FITs, risk level for CRC (i.e., family history or previous adenoma), time since previous colonoscopy, or FIT. Individual differences in psychological measures will be collected to identify any measures that are likely to predict surveillance preferences: fear of cancer, quality of life, trust in healthcare, perceived convenience of FIT versus colonoscopy, dissatisfaction with previous procedures, relative differences in perceived response efficacy between the two, anxiety about change, and consumer health activation, and self-efficacy for FIT and colonoscopy. Health activation measurement will be with the Consumer Health Activation index (CHAI) [39] which comprises 10 items designed to assess a consumer’s health activation level, where high health activation is positively associated with health self-management [25]. An independent samples *t*-test will compare satisfaction between subjects offered the extended or standard surveillance protocol. A multivariable logistic regression analysis will be applied to determine predictors of preferences for surveillance type and frequency. Independent variables that are not linear on the log-odds scale will be categorized or transformed.

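### The willingness exclusion can remove randomised participants after they learn their arm, mainly those refusing delay, and so conflicts with the primary intention-to-treat analysis

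*Protocol article*

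**What the plan says.** Study schedule (timing of events) sets the rule: "Any participant not willing to be assigned to the delegated study arm, either before or after informed consent, will be excluded from the study". The same section continues: "If the patient consents to be enrolled and then subsequently withdraws, they will still have their colonoscopy following guideline recommendations".

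The order of events is given there and in Table 1. Consent comes first, surveys 1 and 2 follow at month -3, and randomisation is at month -2. Then: "Upon return of surveys 1 and 2, all participants will be sent a letter by mail informing them of their randomization arm".

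Enrolment criteria adds two facts that decide who is likely to refuse. On blinding: "Participants and referring endoscopists will not be blinded to the randomization arm". On the control arm: "Those not randomized to the Intervention group will receive standard clinical care".

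Under Advanced neoplasia incidence, colonoscopy at a time other than the allocated one is treated as non-adherence. It is to be examined by per-protocol, modified intention-to-treat or as-treated analyses, "alongside the primary intention-to-treat analysis".

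Outcome parameters lists as a secondary outcome: "Acceptability to consumers of changes to the surveillance strategies and the variables that predict this attitude". Consumer acceptability adds a t-test that "will compare satisfaction between subjects offered the extended or standard surveillance protocol".

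**The concern.** A participant can object to a particular allocated arm only once it is known, which is after randomisation. The exclusion has no cut-off at randomisation, so it covers such people. A person in the control arm has no delay to refuse, whereas a person in the intervention arm has been told to wait one or two more years. Controls with the same reluctance stay in the trial, and their counterparts in the intervention arm leave.

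An intention-to-treat analysis keeps people in the arm to which they were randomised whether or not they accept it. Followed literally, the exclusion would prevent that. If refusers differ from acceptors in their risk of advanced neoplasia, the two arms are no longer comparable on the endpoint meant to show that delay is safe. A refusal of delay is also direct evidence on acceptability, yet refusals are not listed as something to be reported. The Discussion acknowledges self-selection among people who choose to enrol, but not loss after allocation.

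**Working it through.** **Reading the sections together.**

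1. Consent, surveys 1 and 2, randomisation, arm letter (Study schedule, Table 1). The exclusion applies after consent without limit, so it covers the period after the letter.
2. A randomised participant who refuses delay and has the guideline colonoscopy has an off-schedule procedure for the allocated arm. Advanced neoplasia incidence treats that as non-adherence within an intention-to-treat framework; Study schedule treats it as exclusion. Both cannot be followed.
3. The outcome for such a person can exist, because Study schedule still provides the colonoscopy.

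**The plan's own figure.** Inputs from Sample size: control 9%, difference 5 points (so 14%), two-sided alpha 0.05, power 80%, pooled Z test, 672 per group.

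n = [1.960 × √(2 × 0.115 × 0.885) + 0.842 × √(0.09 × 0.91 + 0.14 × 0.86)]² / 0.05² = 638 per group.

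A continuity correction gives 678. The stated 672 equals 638/0.95, although the text states no 5% allowance. Power at 672 per group is 82.0%. The figure is sound enough to use as the reference and is not in dispute here.

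**Bias if refusers are dropped from the intervention arm.** The documents give no refusal rate u and no refuser risk r; both are assumptions. With a true rate of 9% in both arms, the rate left in the intervention arm is (0.09 − u × r)/(1 − u).

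| u | r | Remaining rate | Bias (points) |
|---|---|---|---|
| 5% | 13.5% | (0.09 − 0.00675)/0.95 = 8.76% | −0.24 |
| 10% | 15% | (0.09 − 0.015)/0.90 = 8.3% | −0.7 |
| 15% | 20% | (0.09 − 0.03)/0.85 = 7.1% | −1.9 |
| 10% | 5% | (0.09 − 0.005)/0.90 = 9.4% | +0.4 |

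The last row shows the reversal when refusers are at lower risk.

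**Effect on a real difference of 9% against 14%.** Suppose refusers have 1.5 times the acceptors' risk (assumed). At 10% refusal the acceptors' rate is 0.14/(0.90 + 0.10 × 1.5) = 13.3%. The apparent difference is 4.3 points and power is 69%. At 20% refusal the rate is 0.14/(0.80 + 0.20 × 1.5) = 12.7%, the difference 3.7 points and power 55%. The lost numbers alone matter little: with no selection, 605 against 672 at 10% refusal still gives 80% power.

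**Effect of keeping refusers.** If those refusing have an on-time colonoscopy at 9% risk, the intervention rate is 0.14 × (1 − u) + 0.09 × u.

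| u (assumed) | Intervention rate | Power at 672 per group | n per group for 80% power |
|---|---|---|---|
| 5% | 13.75% | 78% | 701 |
| 10% | 13.5% | 74% | 773 |

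**Acceptability.** Surveys 1 and 2 (preferences, psychological predictors, choice experiment) are returned before the arm is known, so later refusers have already supplied them. Satisfaction is asked in survey 5 and the choice experiment repeated in survey 6, both after colonoscopy. Someone excluded from the study would not supply those.

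**The case against.** The strongest reply is that exclusion from the study may mean only that participation stops. Under Colonoscopy procedure the authors refer expressly to the data analysis when they mean to leave results out. Participants with symptoms are to be withdrawn, yet colonoscopy brought forward for symptoms is handled under the alternative analyses beside intention-to-treat. A full analysis plan may settle the analysis sets. This reading is possible, but the article does not state it. Under Interval FIT Hb analysis the authors say that FIT-positive participants stay enrolled, so they do mark retention when they intend it. A narrower reading, that the rule covers only people unwilling to be randomised at all, is also open, but the text sets no such limit.

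Three stronger inferences are tempting, and the documents do not support them.

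- A reader might infer that acceptability is measured only in those who accept delay. It is not: surveys 1 and 2 precede disclosure. Only the later measures are exposed, unless exclusion also discards the baseline surveys.
- A reader might infer that only the intervention arm can lose people. The rule is worded for both arms, and a control participant who wanted delay could leave too. The imbalance is expected, not absolute.
- A reader might infer that the bias must make delay look safer. Its direction depends on refusers' risk, which is unknown. The −1.9 point case needs refusers at 20% against 7.1% in acceptors, about 2.8 times the risk, and nothing in the documents supports that ratio.

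It is also fair to say that refusals may be few, since participants are told before enrolment that allocation is random and the Discussion expects enrollees to be comfortable with delay.

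**Conclusion.** The concern holds as a conflict between two stated rules. As written, the exclusion reaches randomised participants who know their arm and cannot be reconciled with the primary intention-to-treat analysis. It is likely to act mainly on intervention participants who refuse delay, and it can bias the primary comparison in either direction. The assumed cases range from +0.4 to −1.9 points against a design difference of 5 points; they are illustrations, not estimates. Measures of satisfaction and preference after allocation would miss refusers, while the baseline acceptability data need not be affected. The conflict should be resolved in the protocol, because results not collected from excluded participants may be impossible to recover at analysis.

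**What to change.** Three changes to the protocol text:

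1. Limit the willingness exclusion to the period before randomisation.
2. State that every randomised participant stays in the allocated arm for the intention-to-treat analysis, using the result of the guideline colonoscopy that Study schedule already provides. Seek consent to use that result from anyone who stops other study procedures.
3. Report refusals after randomisation by arm, as an acceptability result.

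No clinical procedure changes. The cost is some wording in the protocol and consent form, and dilution of the contrast. At the assumed refusal rates of 5% and 10%, power falls from 82% to about 78% and 74%. Dilution also pulls the observed difference toward zero, to 4.5 points at 10% refusal, so the gain is a comparison that respects randomisation and not a larger signal. The protocol should state this, consider whether 672 per group still suffices, and read the planned per-protocol analysis alongside, noting that it too is open to selection by refusal.

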### Interval FIT Hb analysis

Fecal Hb analysis in the interval between the delayed colonoscopies for participants randomized to the intervention arm will be performed using two-sample OC-sensor FIT. Testing kits will be provided to participants by mail, with instructions for collection as previously described [36]. Participants will be asked to return the collected fecal samples in the FIT collection devices by mail, within 2 weeks of the first fecal sample being collected. Assessment of fecal Hb concentrations will be performed as per the manufacturer instructions [36]. In the event the FIT result is positive (over 20 µg Hb/g feces or 100 ng/mL of OC-sensor sample buffer in either fecal sample), the surveillance colonoscopy will be scheduled as soon as possible, and the delayed procedure date will be abandoned. These participants will remain enrolled and complete the follow-up survey as dictated in the study schedule.

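### Table 1 spaces surveys 5 and 6 unequally after colonoscopy (7 and 8 months for controls, 1 and 2 in the 3-year intervention group), against the one month that the text gives for survey 5

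*Protocol article*

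**What the plan says.** The Study schedule section places survey 5, which carries test preference, QOL and satisfaction with the procedure, by reference to the colonoscopy and without distinction by arm: "Within the follow-up test preference and QOL survey (survey 5), which is provided one month after colonoscopy". Survey 6, the repeat discrete choice experiment (DCE), has no month in the text. It is to be done "once the patients have been informed of pathology findings from their colonoscopy".

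Table 1 in the same section uses a different clock. Its caption reads "Study schedule listing the timing of events (in months) relative to the guideline recommended colonoscopy due date specified at the time of enrolment". Its columns run: screening, surveys 1 and 2, randomization, on-time colonoscopy, FIT 1, FIT 2, delayed colonoscopy, survey 5, survey 6. The control row reads "Control − 6 − 3 − 2 0 N/A N/A N/A 7 8", which puts the colonoscopy at month 0 and the two follow-up surveys at months 7 and 8. In the 3-year intervention row the delayed colonoscopy is at month 12 and the surveys are at months 13 and 14. The 5-year intervention row reads "Intervention: 5-year surveillance − 6 − 3 − 2 N/A 0 12 24 31 32", which puts the delayed colonoscopy at month 24 and the surveys at months 31 and 32.

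The Survey completion section says that surveys are mailed at the times in Table 1. For participants whose colonoscopy is brought forward by a positive interval FIT, the Interval FIT Hb analysis section says: "These participants will remain enrolled and complete the follow-up survey as dictated in the study schedule". The Consumer acceptability section plans that an independent-samples *t* "test will compare satisfaction between subjects offered the extended or standard surveillance protocol". The Enrolment criteria section accepts a colonoscopy within 6 months of its set time.

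**The concern.** Two current instructions for survey 5 disagree, and the one that governs mailing does not treat the groups alike. Satisfaction with a procedure is a recalled judgement, and preference and DCE answers may also shift as the procedure and its findings recede. If one arm is asked a month afterwards and the other seven months afterwards, an unadjusted comparison of satisfaction cannot separate the effect of the extended interval from the effect of time since colonoscopy. Timing lost at mailing cannot be recovered in the analysis.

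The due-date clock raises a second problem. A colonoscopy brought forward by a positive FIT moves the procedure but not the Table 1 survey months, and this can happen only in the intervention arm.

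**Working it through.** **Inputs.** Scheduled colonoscopy, survey 5 and survey 6 months come from Table 1. The one-month lag for survey 5 is from the Study schedule text, and the 6-month window is from Enrolment criteria.

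**Step 1: scheduled lag = survey month − scheduled colonoscopy month.**

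| Group | Colonoscopy | Survey 5 | Lag | Survey 6 | Lag |
|---|---|---|---|---|---|
| Control | 0 | 7 | 7 − 0 = 7 | 8 | 8 − 0 = 8 |
| Intervention, 3-year | 12 | 13 | 13 − 12 = 1 | 14 | 14 − 12 = 2 |
| Intervention, 5-year | 24 | 31 | 31 − 24 = 7 | 32 | 32 − 24 = 8 |

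Only the 3-year intervention row reproduces the text's one month for survey 5.

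**Step 2: does any single rule generate the survey 5 column?**

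| Rule | Control | 3-year | 5-year |
|---|---|---|---|
| Colonoscopy + 1 | 0 + 1 = 1 | 12 + 1 = 13 | 24 + 1 = 25 |
| Colonoscopy + 6-month window + 1 | 0 + 6 + 1 = 7 | 12 + 6 + 1 = 19 | 24 + 6 + 1 = 31 |
| Table 1 as printed | 7 | 13 | 31 |

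The first rule fits only the 3-year row. The second fits only the other two rows. Either rule, applied throughout, would give equal scheduled lags in all groups.

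**Step 3: imbalance between arms, with colonoscopies on the scheduled month.**

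- 3-year stratum: 7 − 1 = 6 months for survey 5, and 8 − 2 = 6 months for survey 6.
- 5-year stratum: 7 − 7 = 0 and 8 − 8 = 0.
- Pooled, with *f* the share of participants on a 3-year interval: the mean intervention lag to survey 5 is *f* × 1 + (1 − *f*) × 7 = 7 − 6*f*. The control mean is 7, so the difference is 6*f*.

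The article does not give *f*. Over an assumed range:

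| *f* (assumed) | Difference in mean lag, control − intervention |
|---|---|
| 25% | 6 × 0.25 = 1.5 months |
| 50% | 6 × 0.50 = 3.0 months |
| 75% | 6 × 0.75 = 4.5 months |

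**Step 4: FIT-triggered colonoscopy, literal reading.** FIT 1 is at month 0. Assume a positive result leads to colonoscopy near month 1 (the text says only that it is scheduled as soon as possible). If survey 5 stays at its Table 1 month, the lag is 13 − 1 = 12 months on the 3-year schedule and 31 − 1 = 30 months on the 5-year schedule.

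**The case against.** The best defence is that Table 1 never claims to give lags from the actual procedure. It counts from the due date, and a colonoscopy up to 6 months from its set time is acceptable. Months 7 and 31 are then one month after the end of the window, which would agree with the text for a late procedure. This may well be how those figures arose. But the article does not say so, and the 3-year row would then read 19, not 13. As printed, an acceptable 3-year delayed colonoscopy done after month 13 (the window runs to 12 + 6 = 18) would come after its own satisfaction survey. The window explains two rows and leaves the table inconsistent.

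A second defence is that the text ties both surveys to events: survey 5 to the colonoscopy, survey 6 to the pathology results. If staff mail by the text, the imbalance does not arise. That is true, and it makes the bias conditional. But the Survey completion section points staff to Table 1.

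Several limits stand in full:

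- The text gives survey 6 no month, so its printed times do not contradict the text. The fault there is the unequal lag within the table.
- QOL is also collected in survey 3, 4 weeks after the procedure for everyone, so that outcome has a source outside Table 1. The article describes no comparable second source after the procedure for satisfaction, test preference or the DCE.
- The 12- and 30-month figures are worst cases. They need a positive first FIT, a prompt colonoscopy, and surveys held to the abandoned date despite the one-month wording.

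**Conclusion.** The point holds as an internal inconsistency in the survey schedule, with a conditional consequence for a planned comparison. Table 1 and the text disagree on survey 5 for two of three groups, and no single rule produces the printed months. If Table 1 is followed and colonoscopies occur on schedule, controls in the 3-year stratum answer surveys 5 and 6 about 6 months later after their procedure than intervention participants in that stratum. Pooled, the difference is 6 months times the 3-year share, or 1.5 to 4.5 months for assumed shares of 25% to 75%.

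A reader might infer that every control is surveyed 6 months later than every intervention participant, or that the acceptability comparison is already confounded. The documents do not support either. The 5-year stratum has equal scheduled lags, actual procedures may fall anywhere in the window so individual lags will vary, and the imbalance vanishes if the text's timing is used for all.

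The primary endpoint, advanced neoplasia, is untouched. The exposed outcomes are secondary: satisfaction (the *t*-test), test preference and the follow-up DCE, with QOL only partly exposed. The matter should be corrected before follow-up surveys are mailed.

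**What to change.** Trigger surveys 5 and 6 from each participant's actual colonoscopy date, with the same lag in every group. Survey 5 goes at +1 month, as the text states. Survey 6 goes at one common lag after pathology results have been given; +2 months would keep the one-month step between surveys already in Table 1. State that the same trigger applies when a positive FIT has brought the colonoscopy forward, so that the reference to the study schedule in the Interval FIT Hb analysis section cannot be read as the original due date.

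Correct Table 1 to match, noting that the months apply to on-schedule procedures: surveys 5 and 6 at 1 and 2 (control), 13 and 14 (3-year intervention), 25 and 26 (5-year intervention). A due-date table with the window added throughout (7/8, 19/20, 31/32) would also be consistent in itself, but it would leave the lag dependent on when in the window each procedure fell.

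The cost is one corrected table, one clarifying sentence and a changed mailing trigger. No surveys or participants are added.
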